## Purpose, Primary and Secondary Outcomes

Therefore, we propose to study the clinical and mechanistic effects of the combination of two well-studied interventions—CBT and tDCS—for the treatment of MDD in drug naïve first episode patients. The primary outcome will be the clinical effects (severity of depression/mood amelioration), as measured by the Montgomery-Asberg Depression Rating Scale (MADRS). Secondary outcomes will be resting state and emotional task eliciting EEG, which will be useful simultaneously to understand the neural effects of the intervention, as well as potential response predictors for future trials.

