## Research Question, Aims, Hypothesis

By combining two interventions that showed promising results in MDD (CBT and tDCS), we aim to investigate the clinical and underlying neurophysiological effects in first-episode drug naïve MDD patients. The main research question underlying this proposal is whether tDCS as add-on therapy to CBT in drug naïve, first-episode MDD patients could produce greater significant clinical improvements, as measured by the MADRS, when compared to CBT alone. We hypothesize that the combination of these therapies will produce a synergetic effect in the brain, potentiating the effects of CBT and decreasing the depressive symptomatology as assessed by the MADRS.

A secondary aim will be to perform the dose calculation (number of sessions) required to induce a clinically significant effect (50% decrease in the MADRS score). The underlying hypothesis is that the combination of tDCS with CBT will require a lesser number of sessions in order to elicit this clinical meaningful effect.

The second major scientific question is whether these clinical improvements will be correlated with the rebalancing of the inter-hemispheric asymmetry of EEG alpha activity toward the left hemisphere, as assessed by resting-state and emotional task eliciting-EEG. Here, the hypothesis is that both interventions (combined and alone) will reduce the inter-hemispheric alpha imbalance, as indexed by EEG power; however, that reduction will be more pronounced in the group that received the add-on intervention, as compared to CBT alone.

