### Statistical Analysis

#### Primary Outcome

A mixed model ANOVAs will be used to assess the clinical effects for primary outcome measure (MADRS), with intervention as between subject factor (active vs. sham tDCS), and time as within subject factor (weeks 2, 4, 8, 12, and 6 months). If there are significant baseline differences across the groups, those covariates will be included in the analysis (such as severity, anxiety, and quality of life). If significant main effects and/or interactions arise from the main analysis, *post-hoc* analysis corrected for multiple comparisons will be performed. If our hypothesis of prefrontal inter-hemispheric imbalance (as assessed by alpha power EEG) is confirmed, we will then conduct correlation analysis in order to assess whether these brain signatures correlate to long-term clinical effects in MDD.

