## Discussion

The current study describes a protocol for a parallel randomized, triple-blind, sham controlled clinical trial to test the synergetic clinical and electrophysiology effects of combining cognitive-behavioral therapy with transcranial direct current stimulation in drug-naïve, first-episode MDD patients.

By combining two therapies that have shown promising results in patients with MDD, we expect that the group that received CBT combined with active tDCS will have a greater reduction on MADRS scores, and will require lesser number of sessions in order for the clinical outcome to be reached. This result will have a significant impact since major depression is the second most prevalent mental disorder, which is thought to affect 163 million people worldwide (64). Furthermore, in Portugal, 7% of the population is diagnosed with depression every year (65), and suicide is responsible for more than a thousand deaths annually (66).

Despite the fact that tDCS has some promising effects on mood, it seems that it is in the combination of tDCS with other intervention that the effects are larger. For instance, in the study of Loo et al. (67), which randomized 64 patients to 15 sessions of 2 mA tDCS over 3 weeks and the study of Brunoni et al. (21), which enrolled 120 antidepressant-free patients with moderate and severe depression, tDCS has been shown to be effective in MDD. Moreover, in the study of Brunoni et al. (21), not only active tDCS was superior to sham tDCS but also the combined tDCS/sertraline was significantly more effective than in the other treatment groups in reducing depressive symptoms. Thus, the effects of tDCS seem to be enhanced by the combination with other interventions. This can be particularly important, if patient level data is taken into consideration. In a recent individual patient data meta-analysis (23) tDCS was shown to be less effective in high-resistant patients. This also reinforces the need of improving tDCS techniques so they can be effective in a broader depressed population.

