We also propose to study, as secondary aim, whether CBT combined with tDCS can engage the proposed mechanistic target, of restoring the prefrontal imbalance and connectivity, by changes over resting-state and task-eliciting EEG. This trial will help to evaluate the efficacy of this combined treatment as compared to CBT alone and to evaluate bilateral alpha activity over the prefrontal cortex. Thus, we also expect to demonstrate that these interventions are able to reduce the inter-hemispheric asymmetry of alpha EEG activity toward the left hemisphere reported in patients with depression. We expect that the combined intervention will induce greater asymmetry reduction (at least 50% minimum reduction). We also expect that this inter-hemispheric imbalance reduction will be correlated with mood improvement.

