Therefore, the results of this project will further provide important insights into the mechanisms underlying MDD. In sum, we will be able to study the mechanistic reason underlying differences between the add-on treatment group vs. CBT combined with sham tDCS. We chose a population that is not very well studied, namely patients drug-naïve, first-episode MDD with mild to moderate symptoms, because several studies failed to show the link between decreased left frontal activation and depression. By using resting state EEG, it will be possible to simultaneously understand the neural effects of the intervention, as well as potential response predictors for future trials.

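### The EEG-MADRS association should be estimated with arm in the model: pooled over arms, a correlation can arise from the two expected arm effects alone and cannot support the mechanism claim

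*Protocol article*

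**What the plan says.** The Protocol article's section on research question, aims and hypothesis makes the EEG-mood link the trial's second main question: "whether these clinical improvements will be correlated with the rebalancing of the inter-hemispheric asymmetry of EEG alpha activity toward the left hemisphere". It expects both arms to show less alpha imbalance, but adds that "that reduction will be more pronounced in the group that received the add-on intervention, as compared to CBT alone". The Discussion expects an arm effect on the clinical scale too: "we expect that the group that received CBT combined with active tDCS will have a greater reduction on MADRS scores".

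The method is given in Statistical Analysis, Primary Outcome. On the condition "If our hypothesis of prefrontal inter-hemispheric imbalance (as assessed by alpha power EEG) is confirmed", the text continues: "we will then conduct correlation analysis in order to assess whether these brain signatures correlate to long-term clinical effects in MDD". The same paragraph specifies arm, time and possible covariates for the MADRS mixed-model ANOVA. For the correlation it names no coefficient, arm term or covariate, and it does not say whether the arms are pooled. No other section describes an arm-adjusted or mediation analysis.

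Two Discussion statements rest on this analysis. One is an expectation: "We also expect that this inter-hemispheric imbalance reduction will be correlated with mood improvement". The other is a claim about what the trial can show: "we will be able to study the mechanistic reason underlying differences between the add-on treatment group vs. CBT combined with sham tDCS".

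**The concern.** When treatment shifts two outcomes, patients in the active arm tend to be better on both and patients in the sham arm worse on both. Correlating the two outcomes across all patients picks up this separation between arms. The correlation is then non-zero even if, within each arm, a patient's EEG change says nothing about that patient's mood change. The protocol predicts exactly this pair of arm effects.

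The condition on running the analysis gives no protection. If confirming the EEG hypothesis means finding a larger asymmetry change in the active arm, it selects the trials in which the artefact can arise.

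At stake is the answer to a declared main question. Rebalanced alpha asymmetry could be reported as the reason for tDCS benefit when the data show only that the arms differ on two outcomes.

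**Working it through.** **Inputs from the article.** Total 90, 45 per arm, 1:1 (Participants; Randomization). MADRS effect used for planning d = 0.66, described as the upper 95% confidence limit of a pooled estimate (Sample Size Calculation). Pooled tDCS effect 0.36 (Background). Two-sided 5% level.

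**Assumed input.** The arm effect on asymmetry change. The Discussion expects a reduction of at least 50% but gives no standard deviation, so it cannot be converted to a standardized effect. A range of 0.36 to 1.0 SD is used.

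**The plan's own figure.** For d = 0.66, 80% power and two-sided 5%, the two-sample t-test needs 37.02 per arm, so 38 (power 81.0%). Then 38/(1 − 0.15) = 44.7, so 45. The stated 38 and 45 reproduce.

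**Induced correlation.** Let dM and dE be the arm effects on MADRS and on asymmetry change in within-arm SD units, with equal arms and zero correlation within each arm. The arms then contribute covariance dM·dE/4, and each variance becomes 1 + d²/4, so

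r = (dM·dE/4) / √[(1 + dM²/4)(1 + dE²/4)].

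At dM = 0.66 and dE = 1.0: 0.165 / √(1.1089 × 1.25) = 0.165/1.177 = 0.140.

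At dM = dE = 0.36: 0.0324/1.0324 = 0.031.

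**Rejection rate of the pooled test (Fisher z).** With m = atanh(r)·√(N − 3), the rate is Φ(m − 1.96) + Φ(−m − 1.96).

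For r = 0.140 and N = 90: m = 0.141 × 9.327 = 1.316, giving Φ(−0.644) + Φ(−3.276) = 0.260.

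| Assumed dE | r, dM = 0.36 | rate | r, dM = 0.66 | rate |
|---|---|---|---|---|
| 0.36 | 0.031 | 6.0% | 0.056 | 8.1% |
| 0.5 | 0.043 | 6.9% | 0.076 | 11.0% |
| 0.66 | 0.056 | 8.1% | 0.098 | 15.1% |
| 0.8 | 0.066 | 9.4% | 0.116 | 19.3% |
| 1.0 | 0.079 | 11.5% | 0.140 | 26.0% |

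**Check by simulation.** With 20,000 trials per setting, the pooled rates agree with the table to within about one percentage point. With arm partialled out, the rate is about 5% in every setting.

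**Fewer patients.** With 76 patients and dM = 0.66, the pooled rate is 10.0% at dE = 0.5 and 22.6% at dE = 1.0.

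**Restricting to trials with a significant arm difference in asymmetry** (one reading of the stated condition; N = 90, dM = 0.66). The pooled rate is 13.6% at dE = 0.5, 16.4% at 0.66 and 26.7% at 1.0. The arm-adjusted rate stays near 5%.

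**Where no inflation arises.** If dM or dE is zero, r = 0 and the test, run in every trial, keeps 5%. If the EEG measure is baseline asymmetry, randomization makes it independent of arm, so this route to a correlation is closed.

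**The case against.** The strongest reply is that the article does not state a pooled, unadjusted correlation. It is a condensed text, its analysis plan is not shown, and the choice between a simple and a partial correlation is often left to that plan. This stands in part: pooling is inferred. But the paragraph specifies arm and covariates for the ANOVA and then names an unqualified correlation, whose ordinary meaning is the simple one. The gap between that method and the Discussion's claim about the reason for the arm difference is in the article itself.

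Second, a reader might infer from the MADRS effect of 0.66 that the false-positive rate simply is 11% to 26%. The documents do not support that. It needs asymmetry effects of 0.5 to 1.0 SD, which appear nowhere, and a MADRS effect that the protocol itself takes from an upper confidence limit. At the pooled 0.36 the range is about 6% to 12%.

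Third, the pooled correlation is truly non-zero in these settings, so rejecting zero is no error about that quantity. This is right. The rates are false-positive rates only for the hypothesis of no within-arm association. That is nevertheless the hypothesis a patient-level mechanism claim needs.

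Fourth, the brain signatures are not defined in the analysis section. If they meant baseline EEG, the problem would disappear. The aims and the Discussion, however, speak of rebalancing and of imbalance reduction, which are changes.

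Finally, a reader might infer that the same correlation is meant to find predictors of tDCS response, because the article hopes for "potential response predictors for future trials". No section ties that aim to this correlation or claims prediction specific to tDCS, so it is not part of the point.

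**Conclusion.** The point holds as a conditional one. An unadjusted correlation over both arms between change in asymmetry and MADRS improvement would mix arm effects with any patient-level link, and it cannot show why the arms differ. At N = 90, the induced r is at most about 0.14, roughly 2% of variance (0.14² = 0.0196). A nominal 5% test of no within-arm association would reject in about 6% to 26% of trials, against about 5% with arm adjusted for.

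This rests on five assumptions: the arms are pooled; the EEG measure is a change; both arm effects exist; the MADRS effect is 0.36 to 0.66 SD; and the asymmetry effect is 0.36 to 1.0 SD, which the documents do not supply. The analysis is secondary and conditional. The primary MADRS comparison is untouched.

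**What to change.** State that the association between change in alpha asymmetry and MADRS is estimated with arm, baseline MADRS and baseline asymmetry in the model, or as a partial or within-arm correlation. Say explicitly that the EEG measure is the change from baseline. Keep the planned long-term MADRS outcome; week 6 may be added. Word the conclusion as an association between EEG change and mood change, not as the reason for the arm difference.

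An indirect-effect estimate and a test of baseline asymmetry by arm are optional and should be labelled exploratory.

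The cost is a sentence or two of plan wording and slightly more analysis. MADRS and EEG are already scheduled, so no new data are needed. The price is a more modest mechanism claim.

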#### Secondary Outcomes

##### EEG Analysis

To evaluate the degree of coupling between electrode pairs, we will use Magnitude Square Coherence as a pairwise connectivity measurement. For power spectrum, band power, and intraband mean and median analysis of the EEG frequency ranges, we will use the Fast Fourier transformation analysis, which will allow us to determine and measure the amplitude of the predominant EEG frequency, and properties in the time and frequency domains. For these two EEG analysis, we will define the following frequency bands: delta (1–4 Hz), theta (4–8 Hz), alpha (8–13 Hz), and beta (13–30 Hz) and four frequency sub-bands: low-alpha (9-10 Hz), high-alpha (10-12 Hz), low-beta (13-20 Hz), and high-beta (20-30 Hz), which can be obtained by decomposing the raw signal being generated in different areas of the brain.

Independent Component Analysis (ICA) will be used for artifact rejection. EEG changes during task will be assessed via task-related power (TRP)–i.e., TRP at a given electrode will be obtained by subtracting (log-transformed) power during a pre-stimulus reference interval from (log-transformed) power during the task. Power estimates will be obtained by squaring filtered EEG signals and then band power values will be averaged for both the pre-stimulus reference period and the task intervals. Degree of coupling between electrode pairs, will be assessed by using Magnitude Square Coherence as a pair-wise connectivity measurement.

### Ethics and Dissemination

The trial is registered with the U.S. National Library of Medicine Clinical Trials Registry: NCT03548545 (ClinicalTrials.gov) and is approved by the local ethics committee—*Subcomissão de Ética para as Ciências da Vida e da Saúde (SECVS)* – SECVS 174/2017.

### Confidentiality

All participants will be given subject identification codes composed by letters and numbers to which all the data will be linked. The file records that connect each participant to their identification number will be securely kept on University servers during the entire period of the study, and up to 5 years the study has ended.

### Dissemination Policy

Results of this study will be published in peer reviewed journals, and will be disseminated in national and international conferences and in social media. In any of the dissemination procedures, subjects will not be identified or notified about the event.

## Discussion

The current study describes a protocol for a parallel randomized, triple-blind, sham controlled clinical trial to test the synergetic clinical and electrophysiology effects of combining cognitive-behavioral therapy with transcranial direct current stimulation in drug-naïve, first-episode MDD patients.

By combining two therapies that have shown promising results in patients with MDD, we expect that the group that received CBT combined with active tDCS will have a greater reduction on MADRS scores, and will require lesser number of sessions in order for the clinical outcome to be reached. This result will have a significant impact since major depression is the second most prevalent mental disorder, which is thought to affect 163 million people worldwide (64). Furthermore, in Portugal, 7% of the population is diagnosed with depression every year (65), and suicide is responsible for more than a thousand deaths annually (66).

Despite the fact that tDCS has some promising effects on mood, it seems that it is in the combination of tDCS with other intervention that the effects are larger. For instance, in the study of Loo et al. (67), which randomized 64 patients to 15 sessions of 2 mA tDCS over 3 weeks and the study of Brunoni et al. (21), which enrolled 120 antidepressant-free patients with moderate and severe depression, tDCS has been shown to be effective in MDD. Moreover, in the study of Brunoni et al. (21), not only active tDCS was superior to sham tDCS but also the combined tDCS/sertraline was significantly more effective than in the other treatment groups in reducing depressive symptoms. Thus, the effects of tDCS seem to be enhanced by the combination with other interventions. This can be particularly important, if patient level data is taken into consideration. In a recent individual patient data meta-analysis (23) tDCS was shown to be less effective in high-resistant patients. This also reinforces the need of improving tDCS techniques so they can be effective in a broader depressed population.

We also propose to study, as secondary aim, whether CBT combined with tDCS can engage the proposed mechanistic target, of restoring the prefrontal imbalance and connectivity, by changes over resting-state and task-eliciting EEG. This trial will help to evaluate the efficacy of this combined treatment as compared to CBT alone and to evaluate bilateral alpha activity over the prefrontal cortex. Thus, we also expect to demonstrate that these interventions are able to reduce the inter-hemispheric asymmetry of alpha EEG activity toward the left hemisphere reported in patients with depression. We expect that the combined intervention will induce greater asymmetry reduction (at least 50% minimum reduction). We also expect that this inter-hemispheric imbalance reduction will be correlated with mood improvement.

Furthermore, this mechanistic approach is one of the main advantages of the current proposal. For instance, the use of EEG as an adjuvant tool to exclude neurological conditions or to help in the diagnosis of psychiatric disorders is a common practice in the clinical setting. Evidence of abnormal findings are obtained in about 64 to 68% of the EEGs performed in psychiatric patients (68). These results suggest that EEG can be a potential technique to be used as a coadjutant for the diagnosis and prognosis of several psychiatric conditions, with potential reliability to guide neural-based interventions. EEG has been shown to differentiate patients with MDD and non-depressed healthy controls. Numerous studies have shown that depressed individuals present an asymmetry of EEG alpha activity toward the left hemisphere, even among previously depressed individuals when compared to those who have never experienced clinically significant depression (7–9). Some studies have nevertheless failed to show the link between decreased left frontal activation and depression (19). It has been suggested that inconsistencies in this literature may be the result of clinical and/or methodological differences between laboratories, such as the inclusion or exclusion of co-morbidities (such as anxiety disorders), gender related differences, or the choice of EEG reference (9, 69, 70). Nonetheless, there is robust evidence suggesting that EEG alpha asymmetry is present among individuals with present or history of clinical depression, or even susceptibility to develop depression in the future (71). Additionally, alpha power asymmetry-based neurofeedback (NFB), which aims to train patients to increase right-to-left ratio by rebalancing the left hemisphere hypoactivation, has shown promising results in MDD (72, 73).

The advantages of EEG in MDD go far beyond its potential to detect differences between depressed vs. non-depressed individuals. Namely, EEG can be used to detect changes in the EEG patterns after interventions, and as such can be used to determine the efficacy of the intervention or if used also in the baseline, as an outcome predictor (74, 75). Furthermore, EEG is a direct measure of neural activity, it allows for chronometric sensitivity, has the potential to assess local and network effects, it is easy to use, cheap, and non-invasive. By using EEG, it is possible to quantify the electrical activity over specify regions of interest (power and coherence analysis) and, therefore, correlate with symptoms severity and response prognostic to specific treatments. Thus, creating brain based interventions.

These changes in EEG patterns have been used to direct several interventions, such as tDCS or TMS, however most study lack in the assessment of the real changes in EEG activity. For instance, based on this neurobiological basis, the main target for treating depressive symptoms using non-invasive brain stimulation (NIBS) techniques, such as tDCS and TMS, have been both the left (hypoactive) and right (hyperactive) DLPFC, by placing anodal (excitatory) over the left and cathodal (inhibitory) over the right DLPFC (76, 77). Using this mechanistic approach of facilitating the activation of the left DLPFC relative to the right, beneficial emotional, and cognitive effects in MDD were shown emotional and cognitive effects in MDD (18, 78, 79). Moreover, we chose to include adults with first episode of MDD only as to increase homogeneity of our study sample and thus increase internal validity of our findings. There are several advantages of studying the combination of these treatments in first episode MD drug-naive patients, as their brains were not changed by the pharmacological treatments, by the time course of the condition, or by the recurrence of MDD episodes (and other comorbidities). Second, combining tDCS and CBT are two therapies that have been shown to improve MDD. Moreover, tDCS is a safe, of easy administration, and not expensive non-invasive brain stimulation technique that has been shown to be effective in neuromodulating our target mechanism (imbalance over the DLPFC). Also, CBT is the golden standard treatment for MDD and has also shown to be able to neuromodulate brain structures involved in MDD. Thus, if we show that tDCS combined with CBT produce greater significant clinical improvements in MDD, this may reduce the global burden of MDD (for instance, by reducing the number of therapy sessions and the number of relapses and by producing larger long-term effects).

Therefore, the results of this project will further provide important insights into the mechanisms underlying MDD. In sum, we will be able to study the mechanistic reason underlying differences between the add-on treatment group vs. CBT combined with sham tDCS. We chose a population that is not very well studied, namely patients drug-naïve, first-episode MDD with mild to moderate symptoms, because several studies failed to show the link between decreased left frontal activation and depression. By using resting state EEG, it will be possible to simultaneously understand the neural effects of the intervention, as well as potential response predictors for future trials.

